## Abstract

**Background:** Depressive and anxiety disorders are highly prevalent, but only a small percentage (approximately 50%) of patients receive appropriate treatment. Relevant barriers include communication and coordination gaps between different providers that result from the lack of integration between different care-giving systems. Aftercare following inpatient treatment represents one of these gaps because systematic follow-up care does not exist. Case management-based aftercare coordination by phone might be a promising approach to overcoming this gap and improving long-term treatment outcomes. Case management is a patient-centered and situation-based approach comprising systematic tracking and support of patients by a case manager. The aim of this study is to evaluate the effectiveness of aftercare coordination by phone for patients with depressive and anxiety disorders.

**Methods/design:** The effectiveness of aftercare coordination will be investigated in a prospective randomized controlled trial in four psychotherapeutic inpatient routine care units (St. Franziska-Stift Bad Kreuznach, MediClin Seepark Klinik Bad Bodenteich, Segeberger Kliniken Gruppe Bad Segeberg and Luisenklinik Bad Dürkheim). The patients receiving aftercare coordination (intervention group; IG) will be compared with those who receive treatment as usual (TAU control group; CG). Eligible patients will be required to have a diagnosis of an anxiety and/or depressive disorder and a recommendation for follow-up outpatient psychotherapy.

The aftercare coordination consists of six phone contacts at intervals of two weeks that are performed by therapists in the inpatient units. The patients will complete questionnaires at discharge ( $t_1$ ), 3 months after discharge (i.e., at the end of the intervention ( $t_2$ )) and 9 months after discharge ( $t_3$ ). The primary outcome will be change in symptom severity from  $t_1$  to  $t_3$ , the secondary outcomes will be health-related quality of life and the proportion of patients who manage to begin outpatient psychotherapy by  $t_3$ .

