### Methods/design

#### Study design

The study will be performed as prospective multicenter randomized controlled trial (Figure 1). The patients who receive aftercare coordination by phone (IG) will be compared to those who receive TAU without aftercare coordination by phone (CG). Measurements will be performed at three time points in each group. Baseline measures will be taken at discharge from the inpatient treatment (which will be the beginning of the intervention;  $t_1$ ), and two follow-up measures will be taken after 3 months at the end of the intervention ( $t_2$ ) and again 6 months after the end of the intervention (which will be 9 months after discharge from inpatient treatment;  $t_3$ ).

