#### Randomization

The patients will be randomized using a stratified block randomization with randomly varying block size to ensure concealment and equal group sizes, and the randomization will be stratified by the participating clinical units. The randomization will take place at the individual level at the University Medical Center Hamburg-Eppendorf one week before the beginning of the intervention. The allocation schedule was created with a computer program (Microsoft Excel, Windows) by a researcher at the University Medical Center Hamburg-Eppendorf. The therapists will be informed about the randomization outcome prior to the last psychotherapeutic session during inpatient treatment so that they can inform the patients about their group assignment before discharge.

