### Statistical analyses

The primary analysis will focus on the changes in symptom severity from  $t_1$  to  $t_3$  as assessed with the BDI-II. Comparisons between the IG and the CG will be calculated with mixed model analyses of covariance (ANCOVAs) with symptom severity as the dependent variable and gender and initial symptom severity as covariates. An advantage of this method is that it includes all available data even if the data from another time point for a specific person are missing. Other secondary analyses will be performed regarding changes in health-related quality of life, self-efficacy and anxiety symptom severity from  $t_1$  to  $t_2$  and from  $t_1$  to  $t_3$ . Following the intention-to-treat approach (ITT), we will analyze all randomized participants in the primary analysis to avoid biases such as non-random attrition of the participants. Additionally, a sensitivity analysis following the per-protocol approach will be conducted. This analysis will be performed including only the participants that have completed all measurements. To investigate whether the patient characteristics (e.g., age, level of education, and psychosocial treatment before the inpatient treatment) and patient ratings of the therapeutic alliance predict the outcomes

of the aftercare coordination, different regression analysis models will be applied to the primary and secondary outcomes. Process evaluation and data about the patients' satisfaction and acceptance will be investigated via descriptive and qualitative analyses. We will also conduct drop-out analyses to compare the demographic and clinical baseline characteristics of the completers and non-completers ( $t$ - and  $\chi^2$ -tests). The analyses will be conducted with SPSS 21.

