#### Power calculation

We expect a moderate effect size, which is defined as  $f = 0.25$  according to Cohen [35], for the primary outcome because recent studies that have investigated aftercare programs have reported moderate effect sizes in terms of changes in symptom severity (e.g., depressiveness) [36]. We expect a reduction of the error variance of approximately 30% due to the inclusion of initial symptom severity (BDI at  $t_1$ ) as a covariate (which can be expected to be uncorrelated with the study conditions due to the randomization). These considerations lead to an adjusted effect size of  $f = 0.29$ . To detect a moderate effect between the intervention and control groups in terms of the symptom severity with a power of 80% and an  $\alpha$  of 0.05, a sample size of  $N = 96$  (48 per group) is required. Based on an expected dropout rate of approximately 50% from baseline ( $t_1$ ) to 9 months of follow-up ( $t_3$ ), we aim to include a sample of  $N = 192$  (96 per group) to perform the per-protocol analysis with a sufficient sample size.

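### With t1 BDI-II as a covariate, the primary mixed model keeps patients who lack t2 or t3 but not those who lack t1, so it does not deliver the promised analysis of all randomised participants

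*Protocol*

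**What the plan says.** The Statistical analyses section compares the arms by mixed-model ANCOVA "with symptom severity as the dependent variable and gender and initial symptom severity as covariates". The Power calculation section identifies that covariate: it expects about 30% less error variance "due to the inclusion of initial symptom severity (BDI at" t1).

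The Statistical analyses section then makes two statements about who is analysed. It describes as an advantage of the method that "it includes all available data even if the data from another time point for a specific person are missing". It also says, under intention to treat, that "we will analyze all randomized participants in the primary analysis to avoid biases such as non-random attrition of the participants".

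The order of events comes from other sections:

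- Randomization: allocation takes place "one week before the beginning of the intervention", and therapists learn the result before the last inpatient session "so that they can inform the patients about their group assignment before discharge".
- Study design: "Baseline measures will be taken at discharge from the inpatient treatment", and discharge is also the start of the intervention.
- Abstract: t1 is a patient questionnaire ("The patients will complete questionnaires at discharge").

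The protocol does not say what happens to a randomised patient with no t1 BDI-II.

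**The concern.** In many trials baseline is measured before randomisation, and a missing baseline covariate hardly arises. Here the order is reversed. A patient can be randomised, be told the arm, and then not return the t1 questionnaire. The covariate is then missing, and every row for that patient is removed, including any observed t2 or t3 BDI-II.

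The exclusion would depend on a variable collected after randomisation and possibly after disclosure of the arm. The protocol gives protection against non-random attrition as its reason for intention to treat, and this step lets such attrition back in. At stake are some observed primary outcomes and the accuracy of the intention-to-treat label.

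**Working it through.** **Which patients enter the model.** Take t2 and t3 as outcome rows and t1 as covariate:

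| Patient has | Enters the model? |
|---|---|
| t1, t2, t3 | yes |
| t1 and one of t2, t3 | yes, as the protocol says |
| t1 only | no outcome row |
| t2 and/or t3, no t1 | removed, although outcomes were observed |

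Entering t1 as an outcome row as well would not help, because the covariate would still be missing. A change score from t1 needs t1 too.

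In an illustrative data set of 192 patients, 15 lacked t1 and 131 had some follow-up. Of those 131, 122 entered the model. The other 9 were removed only because t1 was missing.

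**The protocol's own figures.** 0.25/√(1 − 0.30) = 0.2988, which the protocol gives as 0.29. With f = 0.29, α = 0.05 and two groups, a noncentral F calculation gives N = 96 (power 80.3%), and 96/(1 − 0.50) = 192. The sample size reproduces and is not in dispute. The 50% dropout is counted from t1, so nothing is allowed for loss between randomisation and t1.

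**Precision lost if patients without t1 are removed.**

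Inputs from the protocol: 192 randomised (96 per arm), 50% lost by t3, and 30% of variance explained by t1. The last gives a t1–t3 correlation of √0.30 = 0.548.

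Assumptions:

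- Half of those lost by t3 also miss t2, so per arm 48 have t2 and t3, 24 have t2 only and 24 have neither.
- Correlations are 0.60 for t1–t2 and 0.65 for t2–t3.
- Variances are 1 and the covariance is known. Gender is left out.
- A share m lacks t1, independently of later dropout.

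Given t1, the variance of t2 is 1 − 0.36 = 0.64, the variance of t3 is 1 − 0.30 = 0.70, and their covariance is 0.65 − 0.60 × 0.548 = 0.321. The squared partial correlation is ρ² = 0.321²/(0.64 × 0.70) = 0.2305.

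*Patients without t1 removed:*

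Var = 2 × 0.70 × [(1 − ρ²)/(48(1 − m)) + ρ²/(72(1 − m))] = 0.02693/(1 − m)

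*Patients without t1 kept:* add the information on the t2 and t3 contrasts from patients with t1 (conditional covariance) to that from patients without t1 (marginal covariance), then invert. At m = 0.10, per arm:

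- with t1: 43.2 patients with both visits and 21.6 with t2 only
- without t1: 4.8 and 2.4
- summed information matrix: [132.18, −45.68; −45.68, 88.52], determinant about 9,614
- Var = 2 × 132.18/9,614 = 0.02750

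| Missing t1 | In model, removed (144 × (1 − m)) | Observed t3 values discarded (96 × m) | SE removed | SE kept | Variance ratio |
|---|---|---|---|---|---|
| 0% | 144 | 0 | 0.1641 | 0.1641 | 1.00 |
| 5% | 137 | 5 | 0.1684 | 0.1649 | 1.042 |
| 10% | 130 | 10 | 0.1730 | 0.1658 | 1.088 |
| 20% | 115 | 19 | 0.1835 | 0.1677 | 1.197 |

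The standard error itself rises by about 2%, 4% or 9%.

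**On the protocol's own power basis** (f = 0.29, patients observed at t3 only), the number at t3 falls from 96 to 91, 86 or 77. Power falls from 80.3% to 78.1%, 75.7% or 70.9%.

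**The case against.** Five points can be made for the protocol.

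1. **Handling of a missing covariate belongs in the SAP.** The SAP is not shown and may impute t1. The protocol never mentions listwise deletion. So it cannot be said flatly that every patient without t1 will be dropped; that holds only if nothing is done. What stands is that the protocol credits full inclusion to the method itself, and for t1 the method does not have that property.

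2. **The sentence on available data is true where loss is expected.** It is right for t2 and t3, where the 50% dropout is placed. This stands, and the fault is confined to t1.

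3. **The size has no anchor in the protocol.** The missing-t1 rates and two of the three correlations are assumptions. If patients who skip t1 also return fewer follow-ups, less is lost than the table shows. Both stand.

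4. **The count of 144 out of 192 with complete t1 is not caused by the covariate.** A reader might take it as the size of the defect. It reflects patients with neither t2 nor t3, and neither remedy recovers information on the effect from them. It bears only on the wording of the intention-to-treat promise.

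5. **The remedies assume that t1 is unaffected by allocation, which early disclosure puts in doubt.** This stands as a limit. The Power calculation section already assumes t1 to be uncorrelated with arm because of randomisation. Randomisation alone does not secure that for a measure taken after disclosure.

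**Conclusion.** The point holds in a limited form. As written, the primary model keeps randomised patients with a missing t2 or t3 and not those with a missing t1. The order of randomisation and t1 makes a missing t1 a post-randomisation loss, so the statement that all randomised participants are analysed is not secured by the method given as the reason for it.

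The size is unknown. It is nil if t1 is complete. Under the stated assumptions the variance of the t3 contrast is about 4%, 9% or 20% larger at 5%, 10% or 20% missing t1. These are losses of precision only.

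A reader might infer that the primary result will be biased because t1 is lost unequally between arms. The documents do not support that. They give no sign of unequal loss, and they do not fix whether the questionnaire is completed before or after the patient learns the arm. Such bias is possible, not shown. Nor does the point disturb N = 96 or N = 192.

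**What to change.** In the Statistical analyses section, state that randomised patients with a missing t1 BDI-II stay in the primary model, by one of two routes:

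- keep the ANCOVA and impute a missing t1 without regard to arm; or
- fit t1, t2 and t3 as outcomes in one mixed model with a common t1 mean for both arms, and take the arm contrast at t3 as the primary test.

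The first is the smaller change. The precision figures above refer to the second; the gain from imputation was not computed.

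Reword the intention-to-treat sentence. It should say that patients with neither t2 nor t3 add no information on the effect, and that the analysis assumes data missing at random.

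The cost is analysis work and wording only, with no new visits, data or patients. Either model can be fitted with standard mixed-model software. The small downside is that both routes assume t1 is unaffected by allocation, as the Power calculation section already does. Compare t1 by arm as a check.

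### The ITT mixed model is said to avoid bias from non-random attrition, but it does so only under missing at random, which the completers-only sensitivity analysis cannot probe

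*Protocol*

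**What the plan says.** The primary outcome is change in BDI-II from discharge (t1) to 9 months (t3), with a measurement between at 3 months (t2). The protocol's Statistical analyses section specifies "mixed model analyses of covariance (ANCOVAs) with symptom severity as the dependent variable and gender and initial symptom severity as covariates" and gives as an advantage that "it includes all available data even if the data from another time point for a specific person are missing". It then adds the intention-to-treat rationale: "we will analyze all randomized participants in the primary analysis to avoid biases such as non-random attrition of the participants". It states no condition on why data are missing.

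One sensitivity analysis follows: "Additionally, a sensitivity analysis following the per-protocol approach will be conducted". Despite its label, its population is defined by returned questionnaires and not by adherence to the intervention: "This analysis will be performed including only the participants that have completed all measurements". There is also a descriptive check: "We will also conduct drop-out analyses to compare the demographic and clinical baseline characteristics of the completers and non-completers".

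Power calculation gives the scale of the problem: "Based on an expected dropout rate of approximately 50% from baseline" to t3. The sample is doubled from 96 to 192 so that the completer analysis is large enough.

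**The concern.** A likelihood-based mixed model that uses every observed score is valid if data are missing at random (MAR). That means that, given t1, any observed t2, gender and arm, dropout does not depend on the score that was not seen. If patients stop returning questionnaires because they have relapsed since the last one, that condition fails and the arm difference at t3 can be biased. Keeping everyone randomised in the analysis set does not change this. The protocol therefore presents as settled something that rests on an unstated assumption.

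The named sensitivity analysis does not help. The completer comparison at t3 adjusts for t1 and gender but makes no use of the t2 scores of those who left. It therefore needs dropout to be unrelated to t3 given baseline and arm alone, which is a stricter condition than MAR. When dropout depends on unseen t3 scores, both analyses tend to be wrong in the same direction, and their agreement would look like robustness. Because the trial is sized for the completer analysis, readers are likely to give that agreement weight.

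**Working it through.** **Inputs from the protocol (Power calculation).** f = 0.25 before adjustment, so d = 2 × 0.25 = 0.50; adjusted f = 0.29; power 80%; alpha 0.05; two equal groups; about 50% dropout by t3.

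**The plan's own figures.** A two-group F test with noncentrality N × f² and f = 0.29 reaches power 0.803 at N = 96. Then 96 / (1 − 0.5) = 192. Both figures reproduce. Expected missing t3 scores: 192 − 96 = 96.

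**Delta adjustment.** Let p be the fraction missing at t3 in an arm, and δ the amount by which its missing patients are worse than MAR predicts, in SD units. The MAR-based arm mean is too favourable by p × δ, so

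overstatement of benefit = p(IG) × δ(IG) − p(CG) × δ(CG),

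where IG is the intervention group and CG the control group. The protocol gives no δ and no dropout by arm, so these values are assumed:

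- 50% missing in both arms, shift in IG only: 0.5 × 0.2 = 0.10; 0.5 × 0.3 = 0.15; 0.5 × 0.5 = 0.25 SD. Against d = 0.50 this is 20%, 30% and 50%.
- 50% missing in both arms, equal shift: 0.5δ − 0.5δ = 0.
- IG 40%, CG 60%, equal shift of 0.5: 0.20 − 0.30 = −0.10 SD. The benefit is understated.
- IG 60%, CG 40%, equal shift of 0.5: 0.30 − 0.20 = +0.10 SD.

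**Could this change a conclusion?** With 48 completers per arm, the smallest significant difference is about 1.9855 × √(2/48) = 0.405 residual SD. The planned effect in those units is 2 × 0.29 = 0.58. On the unadjusted scale the threshold is 0.405 / 0.58 × 0.50 = 0.349 SD. An estimate exactly at 0.50 therefore has a margin of 0.50 − 0.349 = 0.151 SD. An IG-only shift of 0.151 / 0.5 = about 0.30 SD uses it up. This takes the precision as that of 96 completers, so it is approximate.

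**Do the two planned analyses diverge when they should?** Large-sample simulation with 200,000 per arm and a true effect of 0. Assumed correlations are 0.60 (t1–t2), 0.55 (t1–t3) and 0.65 (t2–t3). The assumed log-odds of dropout is 0.8 per SD, with 50% dropout at t3 and t1 and t2 fully observed. Negative values are a false benefit, in SD.

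| Dropout driven by | Mixed model | Completers |
|---|---|---|
| Observed t2, IG only (MAR) | 0.004 | −0.115 |
| Unseen t3, IG only | −0.199 | −0.253 |
| Unseen t3, opposite directions by arm | −0.404 | −0.510 |
| Unseen t3, same in both arms | 0.001 | −0.001 |

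In the second and third rows both analyses show a similar false benefit. In the first row they disagree although the mixed model is right. With the same mechanism in both arms and a true effect of 0.50, the estimates were 0.464 and 0.452, a mild understatement by both.

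**The case against.** The primary estimator is a standard choice for this setting. Attrition that depends on observed scores is also non-random, and the first row of the table shows the mixed model dealing with it where completers fail. A reader might infer that the model gives no protection against non-random attrition. That is not supported: the sentence is overstated, not empty.

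A statistical analysis plan that is not shown may add sensitivity analyses, and the protocol does not say that the completer analysis is meant as a test of MAR. Both points are fair. They limit the remark about one sensitivity analysis to this document, but they do not make the stated rationale correct.

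Three further inferences go beyond the documents. The first is that the baseline comparison of completers and non-completers will be pooled, or that dropout by arm will go unreported; the protocol is silent on both. What can be said is that a baseline comparison cannot detect dropout tied to unseen t3 scores and does not re-estimate the treatment effect. The second is that bias will favour the intervention. The telephone contact in IG is a reason to expect fewer IG dropouts, which with equal shifts works against IG. The calls also end at 12 weeks, six months before t3, which weakens the case for differential loss there. The third is that treating t1 as an outcome with a common mean (a constrained longitudinal model) would be a remedy because every patient then counts. It still assumes MAR. The arm contrast sits in the distribution of t2 and t3 given t1, so patients with t1 only do not alter it.

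**Conclusion.** The point holds in limited form and should be fixed. The protocol credits its primary analysis with a property that it has only under MAR, does not state that assumption, and names a sensitivity analysis that cannot probe departures from it. About half of the primary outcome values are expected to be missing.

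The possible size is material: 0.10 to 0.25 SD, or 20% to 50% of the planned d = 0.50, if IG dropouts alone are 0.2 to 0.5 SD worse than MAR predicts. These figures rest on assumed shifts and dropout patterns, none of which is in the protocol. The bias is zero with equal shift and equal dropout in both arms, and it reverses with equal shift and lower dropout in IG. The documents therefore support the conclusion that the result is exposed to an untested assumption, and not that it will be biased in a known direction or that the mixed model is the wrong primary analysis.

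**What to change.** In the protocol's Statistical analyses section:

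1. Replace the clause on avoiding attrition bias with a statement of the assumption. For example: the primary mixed model uses all observed BDI-II scores and is valid if, given t1, observed t2, gender and arm, dropout does not depend on unobserved scores.
2. Make the missing-data sensitivity analysis a multiple imputation of t3 BDI-II that is delta-adjusted or control-based. Vary delta separately in each arm, from 0 until the conclusion changes (tipping point). Keep the completer analysis as supplementary, and describe it as completers and not per-protocol.
3. State that dropout and its baseline predictors will be reported by arm.

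The cost is wording and some programming, and the sensitivity intervals will be wider than the primary one. Recruitment, visits and sample size do not change.

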#### Power calculation

We expect a moderate effect size, which is defined as  $f = 0.25$  according to Cohen [35], for the primary outcome because recent studies that have investigated aftercare programs have reported moderate effect sizes in terms of changes in symptom severity (e.g., depressiveness) [36]. We expect a reduction of the error variance of approximately 30% due to the inclusion of initial symptom severity (BDI at  $t_1$ ) as a covariate (which can be expected to be uncorrelated with the study conditions due to the randomization). These considerations lead to an adjusted effect size of  $f = 0.29$ . To detect a moderate effect between the intervention and control groups in terms of the symptom severity with a power of 80% and an  $\alpha$  of 0.05, a sample size of  $N = 96$  (48 per group) is required. Based on an expected dropout rate of approximately 50% from baseline ( $t_1$ ) to 9 months of follow-up ( $t_3$ ), we aim to include a sample of  $N = 192$  (96 per group) to perform the per-protocol analysis with a sufficient sample size.

